**Methods and analysis:**

A prospective open cohort study between 1 January 2002 and 30 September 2014 will be based on the general population of people prescribed statins, using records from UK general practices contributing to the Clinical Practice Research Database (CPRD). Participants aged 25–84 years will enter the cohort on the date of their first prescription for a statin and leave on the earliest date of: a cardiovascular event; death; leaving the practice; the last practice upload date or the study end date. If there are no prescriptions within 90 days after the expected finishing date of a prescription, a patient will be defined as a stopper with the discontinuation outcome date as the expected finishing date. Rates of statin discontinuation will be calculated by calendar year, type and dose of statin, age, and morbidities. Cox proportional regression analyses will be run to identify the most important factors associated with discontinuation. Analyses will be run separately for patients without CVD (primary prevention) and with diagnosed CVD (secondary prevention).

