Of these, all seem to have concentrated on patients with already diagnosed CVD, and most were conducted either before the most recent CVD guidelines were issued or UK-derived CVD risk estimation was available. One study, based on Clinical Practice Research Database (CPRD) data, which showed an association between discontinuation and higher total mortality following acute myocardial infarction,^29^ has also provided information about prevalence of comorbidities with respect to different patterns of statin use. Another CPRD study has investigated the factors associated with discontinuation,^30^ but this study was conducted in 2002. This assessed discontinuation risks in a mixed group of patients, but having only 20% of the cohort without diagnosed CVD and following up patients for only 1 year. It has also been noted that further research is needed particularly for patients with low cardiovascular risk.^31^

While there have been observational studies examining the pattern of uptake of statins^32–34^ and of unintended effects from statin use,^35–37^ relatively few studies have examined the discontinuation of statins. We have, therefore, designed a study that will follow statin users in the UK over time, report the rates of stopping for statins with the discontinuation outcome based on prescription data, and look at whether these have changed with time or differ across statin types. The study will also identify any patient groups more likely to stop statins and so possibly increase their risk of CVD.

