To explore the risks of statin discontinuation associated with the covariates, a Cox regression analysis will be undertaken. The model will include age, sex, ethnic group, deprivation quintile, calendar year at the entry to the cohort, baseline CVD risk and the type of statin prescribed at the baseline. Practices might differ in their prescription patterns, so we will account for clustering by practice. We shall calculate the adjusted HRs for baseline characteristics listed above: clinical values; chronic diseases; family history; use of other medications.

The proportional hazards assumption will be checked by using a log-log plot of survival for each variable. Variables which violate the assumption will be included into the model as a stratification factor. If clinically similar variables or categories (for smoking and ethnicity) are associated with similar risks, they will be combined. For continuous variables, recorded values will be used. For non-linear risk associations, fractional polynomials will be used if appropriate.^40^

As BMI, smoking status, systolic blood pressure and cholesterol/HDL ratio may be important patient characteristics but have non-negligible numbers of missing data, multiple imputation will be used to replace missing values.^41^ Five imputed data sets will be created, using multiple chained equations, and Rubin's rules will be used to combine effect estimates and SEs to allow for uncertainty due to imputing missing values. Calendar year; statin stopper status; log of survival time; age; years of records; potentially important characteristics; and type, dose and cumulative exposure to statins will be included in the imputation model.^42^

The main analyses will be run using the multiply imputed data. The least complete data are expected to be for cholesterol/HDL ratio, but information about this test is expected to be important for patient adherence. To ensure the robustness of our findings, we shall also run a sensitivity analysis including only patients with complete data.

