### Additional analyses

Patients might discontinue statins within the first year or after a longer period. The characteristics of these patients might differ, so we shall rerun the main analysis twice, in the first censoring all patients who did not discontinue before the end of year one, and in the second removing all patients who did discontinue before the end of year 1.

Some statin users have discontinuous use, with one or more restarts against a background of fairly continual usage. We shall define a subcohort in the study period for patients who discontinued statins (the outcome date in the main analysis will be their new entry date) and follow them until they have a new statin prescription or they are censored as described in the Study design section. We shall describe how many people restarted statin therapy within the first 6 months, 7–12 months and 12 or more months after their new entry dates using Kaplan-Meier estimates. We shall report descriptive statistics for the covariates listed above both for stoppers who restarted and those who did not.

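### The rule that turns every variable violating proportional hazards into a stratification factor would remove the adjusted HR for any factor of interest it catches

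*Protocol article*

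**What the plan says.** The purpose of the regression is explanatory. The abstract states: "Cox proportional regression analyses will be run to identify the most important factors associated with discontinuation". The Introduction adds: "The study will also identify any patient groups more likely to stop statins and so possibly increase their risk of CVD". The Statistical analysis section puts demographic variables, entry year, baseline CVD risk and initial statin type into the Cox model, with allowance for clustering by practice. It then promises further output: "We shall calculate the adjusted HRs for baseline characteristics listed above", which covers clinical measurements, comorbidities, family history and co-medication.

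The next paragraph sets the check and the remedy. The check is: "The proportional hazards assumption will be checked by using a log-log plot of survival for each variable". The remedy is: "Variables which violate the assumption will be included into the model as a stratification factor". No exception, alternative model or other effect measure is given. The same paragraph says of model form: "For continuous variables, recorded values will be used", with fractional polynomials where the association is not linear.

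The Additional analyses section considers early and late stopping: "The characteristics of these patients might differ, so we shall rerun the main analysis twice". One rerun ends follow-up at one year; the other drops those who stopped in the first year.

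**The concern.** Stratification is a sound remedy for a variable that is only adjusted for and whose own effect nobody needs. Here the variables being checked are the subject of the study. The rule would act on exactly those factors whose association with stopping changes over time, and it would take away their adjusted effect estimate.

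The statin comparison is exposed in the same way. The Sample size calculation is built on HRs between simvastatin and the other statins. If statin type were judged non-proportional, that comparison would have no estimate in the main model. Follow-up can run from January 2002 to September 2014, up to 12.75 years, which leaves room for effects to change.

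**Working it through.** **1. What the study is sized on.** The Sample size calculation gives 5362 observations for an HR of 0.9 or 1.1 and 1196 for an HR of 0.8, at 1% significance and 90% power. Sidedness and allocation are not stated. I assumed a two-sided test and an equal split, and used Schoenfeld's formula:

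D = 4 (z₀.₉₉₅ + z₀.₉₀)² / (ln HR)²

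- 4 × (2.5758 + 1.2816)² = 59.5176
- HR 0.9: 59.5176 / 0.01110084 = 5361.5, rounded up to 5362
- HR 0.8: 59.5176 / 0.0497930 = 1195.3, rounded up to 1196

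Both figures reproduce exactly (one-sided would give 4691 and 1046). The planned statin comparison is therefore a comparison of HRs, and a model that gives no HR for statin type does not deliver it.

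**2. What stratification does.** Let z be the flagged variable, with coefficient γ, and x the other covariates, with coefficients β. With strata defined by z, a stopper i in stratum s contributes

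exp(βxᵢ + γz_s) / Σⱼ exp(βxⱼ + γz_s),

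where the sum runs over patients at risk in the same stratum. Since z_s is the same throughout, exp(γz_s) cancels. The likelihood does not contain γ, so there is no HR, confidence interval or p-value for z from that model.

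**3. Illustration under assumed hazards.** This shows mechanism only; none of the hazards comes from the protocol. I assumed 20,000 patients, two binary factors g and x, a baseline hazard of 0.3 per year in year 1 and 0.1 afterwards, an HR for g of 1.5 in year 1 and 0.8 afterwards, a constant HR of 1.2 for x, and censoring spread evenly over 1 to 12 years.

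| Model | HR for g | HR for x |
|---|---|---|
| Single HR, unstratified | 1.13 | 1.18 |
| Stratified on g | none | 1.18 |
| g as both stratum and covariate | not identified (SE about 2 million, no convergence) | not used |
| Year 1 only | 1.47 | 1.17 |
| After year 1 | 0.82 | 1.19 |

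Stratifying leaves the HR for x intact and gives nothing for g. Splitting time keeps g and shows the reversal that the single HR hides.

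**4. What the plan leaves for a stratified variable.**
- Kaplan-Meier curves and log-rank tests for the covariates (Statistical analysis). These are unadjusted.
- Crude rates. The Statistical analysis section lists entries such as statin type, calendar year, ethnicity, deprivation and CVD risk; the abstract adds age, dose and morbidities. Neither list includes clinical measurements or co-medication.
- The two reruns in Additional analyses. They repeat the main analysis, so on the text they carry the stratification rule with them. Nothing says that a variable stratified in the main model returns as a covariate.

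**5. Continuous variables.** Strata, and log-log curves by group, need categories, whereas the model is to use recorded values. The Covariates section bands age, BMI and QRISK2, so these could be stratified by going back to the bands. It gives none for systolic blood pressure or the cholesterol/HDL ratio.

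**The case against.** The best reply has four parts.

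**Stratifying is standard and harmless to the other HRs.** This is true, as the illustration shows for x. It does not help the variable that has been stratified, and here that variable may be the object of study.

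**Much remains.** A reader might infer that a flagged factor vanishes from the results altogether. The document does not support that: unadjusted curves, log-rank p-values and several crude rates stay. What goes is the adjusted HR in the main model.

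**The year-1 split already supplies the remedy.** This is the strongest part. A factor whose effect changes at around one year may be proportional within each period. If proportionality were checked afresh in each rerun, the factor would remain a covariate and receive two HRs. The split is therefore real mitigation. It is not secure, because the text neither ties the reruns to failure of the assumption nor says whether strata are carried over. The sensitivity analysis limited to five years shortens the horizon but leaves the rule in place.

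**Failure is not shown to be likely.** A reader might infer that the plan itself predicts non-proportional effects. It does not. It expects stopping rates to differ between short-term and long-term users, which by itself is only a changing baseline hazard, and it says that characteristics might differ. A reader might also infer from the roughly 600,000 patients that several main covariates will be flagged. The check is visual, the two prevention groups are analysed separately, and no figure in the document supports a count.

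**Conclusion.** The point holds in conditional form. If a factor of interest is judged to violate proportional hazards, the plan as written removes its adjusted HR from the main model, against the stated aim. If that factor is statin type, it removes the comparison on which the study is sized. For a flagged variable the adjusted estimate is lost completely in that model, by construction. The number of variables affected is unknown.

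The conclusion rests on reading the rule as it stands, with no unstated exception for factors of interest and no unstated re-check in the reruns. It does not rest on the simulated hazards.

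For continuous variables, a reader might infer that the rule cannot be applied at all. That goes too far for age, BMI and QRISK2, which have bands. The conflict with using recorded values is real for all of them, and for systolic blood pressure and cholesterol/HDL ratio the article offers no bands to fall back on.

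**What to change.** In Statistical analysis, limit stratification to nuisance factors. For a factor of interest that fails the check, keep it as a covariate and report its HR for 0–1 year and for beyond 1 year since the first prescription, which is the split already planned, or fit a time-by-covariate term. State in Additional analyses that the same rule applies in both reruns. Continuous variables can then stay as recorded, because no factor of interest has to be banded to form strata.

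The cost is a few sentences, a few extra columns of HRs and somewhat less precise period-specific estimates. No new data are needed.

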### Covariates

To describe the cohort and explore factors associated with the risk of discontinuation, we will consider the following covariates in six major groups. First, demographics will include age (<45; 45–54; 55–64; 65–74; 75–84 years), sex, ethnicity (Caucasian or not recorded, Indian, Pakistani, Bangladeshi, other Asian, Black African, Black Caribbean, Chinese, other ethnic group) and socioeconomic status as measured by the Townsend deprivation score in quintiles. Second, clinical values will include smoking status (non-smoker; ex-smoker; light smoker: <10 cigarettes/day; moderate smoker: 10–19 cigarettes/day; heavy smoker: 20+cigarettes/day; not recorded), body mass index (BMI) in kg/m^2^ (<25; 25–29.9; 30–34.9; 35+, not recorded), systolic blood pressure and cholesterol/high-density lipoprotein (HDL) ratio. Third, chronic diseases will include rheumatoid arthritis, chronic renal disease, liver disease, atrial fibrillation, treated hypertension, cancer, heart failure, diabetes and dementia. Fourth, genetic characteristics will include family history of premature coronary heart disease and diagnosis of familial hypercholesterolaemia. Fifth, other medications will include use of aspirin, use of anticoagulants and—as a proxy for comorbid conditions—the number of different types of medicines having systemic effect and associated with British National Formulary^39^ categories (in each case, at least one prescription in the last year before the entry date). Finally, only for patients in the primary prevention group, their 10-year cardiovascular risk as calculated by the QRISK2–2014 score (banded <5%; 5–9%; 10–14%; 15–19%; 20–24%; 25%+).

For clinical values, the most recently recorded value prior to or at the cohort entry will be used. Chronic diseases will be considered if they were recorded at or before the baseline. For the main analysis, we will use practice-based Townsend deprivation scores as these are available for the whole cohort. We will run an additional analysis on the subset of practices that have consented to link their data to Townsend scores at patient level.

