### Sensitivity analyses

Apart from the two sensitivity analyses already mentioned relating to exposure and missing values, two others will be included. One will be to facilitate comparison with the results of the Zhang *et al*^27^ study for long-term statin discontinuation. In this, we will define an outcome as an absence of any statin prescriptions within the 12 months (365 days) following the expected finishing date of a prescription. As before, the expected last date will also be the date of the outcome. Because of the longer period required for an outcome, for this analysis, we will remove patients with less than 2 years of follow-up records. The other will be run to investigate the influence of possible changes in baseline variables over the full study period, by rerunning the analysis with the follow-up period restricted to 5 years.

A 1% level of statistical significance will be used to allow for multiple comparisons. Stata V.13 will be used for all the analyses.

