### Sample size calculation

All eligible patients will be used in the analyses, allowing investigation of different types of statins and facilitating identification of relevant patient characteristics associated with discontinuation. This approach is particularly important for the smaller group of patients already diagnosed with CVD at baseline.

About one million patients with at least one prescription of statin within the study period are available from the CPRD. Of these, just over one-third had a statin prescription in the past 12 months before the study entry or insufficient data for follow-up. Excluding these will leave about 600 000 patients available for analysis, one-quarter with CVD at the baseline.

For individual drug exposure, 5362 observations will be required to detect a HR of 0.9 or 1.1 at a significance level of 1% with 90% power between simvastatin and other statins. For common drugs such as atorvastatin and rarer drugs such as pravastatin (around 5% of exposure) we will have enough observations for all these drug types for both CVD and non-CVD groups. For rare drugs, such as rosuvastatin (less than 2% of exposure) and fluvastatin (less than 1% exposure), 1196 patients will be required to detect a clinically important HR of 0.8 at a significance level of 1% with 90% of power. We will have enough observations for both the CVD and non-CVD group for rosuvastatin, but only for the non-CVD group for fluvastatin.

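### Combining clinically similar categories when their fitted risks look alike makes the Cox coding depend on the outcome, and small categories (chiefly rare ethnic groups) can lose a valid adjusted HR

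*Protocol article*

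**What the plan says.** Under Covariates the Protocol article lists its categories in advance. Ethnicity has nine: "ethnicity (Caucasian or not recorded, Indian, Pakistani, Bangladeshi, other Asian, Black African, Black Caribbean, Chinese, other ethnic group". Smoking has non-smoker and ex-smoker, then "light smoker: <10 cigarettes/day; moderate smoker: 10–19 cigarettes/day; heavy smoker: 20+cigarettes/day; not recorded".

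Under Statistical analysis it adds a rule for the Cox model: "If clinically similar variables or categories (for smoking and ethnicity) are associated with similar risks, they will be combined". Two conditions must hold: clinical similarity and similar estimated risk. The article puts no threshold or test on the second.

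All analyses run separately for patients with and without CVD at entry. Of about 600 000 patients, "one-quarter with CVD at the baseline". On the error level: "A 1% level of statistical significance will be used to allow for multiple comparisons".

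The same section also plans crude discontinuation rates by ethnic group, and Kaplan-Meier curves and log-rank tests for the covariates.

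**The concern.** One stated aim is to identify patient groups more likely to stop statins. Ethnicity is in the core model, and smoking is among the clinical values that will get adjusted HRs. If two categories are merged because their fitted HRs came out close, the same data have chosen the coding and supplied the estimate, and the usual interval takes no account of the first step.

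This matters most when one category is small. Its HR is imprecise, so it can look similar to a larger neighbour by chance. Once merged, the reported HR is a weighted average dominated by the neighbour, with an interval whose width reflects the combined size. A small group with a modestly higher stopping rate could then be reported with an adjusted HR that is not its own.

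Because the two prevention cohorts are analysed separately, the rule could also give different categories in each, and their HRs would not line up. The article does not say that the coding will be kept the same.

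**Working it through.** **Plan's own figures.** The only design figures concern statin type: "5362 observations will be required to detect a HR of 0.9 or 1.1 at a significance level of 1% with 90% power", and "1196 patients will be required to detect a clinically important HR of 0.8 at a significance level of 1% with 90% of power". The Schoenfeld formula with equal groups, two-sided 1% and 90% power gives the number of events as 4(2.576 + 1.282)² / (log HR)²:
- HR 0.9: 5361.5, rounded up to 5362.
- HR 0.8: 1195.3, rounded up to 1196.

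Both are reproduced. (HR 1.1 would need 6552, which is a separate matter.) This supports reading the 1% level as two-sided and taking precision from event counts. No corresponding figure is given for ethnicity or smoking.

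**Inputs for the merging rule.**
- From the article: the two-condition rule, the 1% level, and a secondary prevention cohort of about 600 000 / 4 = 150 000.
- Assumed: the two categories pass the clinical condition; A has 2000 stoppers and B has 200; the variance of a log HR is 1/stoppers, against a very large reference group; the true HR of B relative to A is 1.10; intervals are 99%, to match the 1% level.
- Assumed readings of similar: (i) p>=0.01, (ii) p>=0.05, (iii) absolute difference in log HR below 0.10.

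**Step 1, chance of merging.** The true difference is log 1.10 = 0.0953. The SE of the observed difference is √(1/2000 + 1/200) = 0.0742, so the standardised difference is 0.0953 / 0.0742 = 1.285. With Φ the normal distribution function:
- (i) Φ(2.576 − 1.285) − Φ(−2.576 − 1.285) = 0.90
- (ii) Φ(1.960 − 1.285) − Φ(−1.960 − 1.285) = 0.75
- (iii) Φ((0.10 − 0.0953)/0.0742) − Φ((−0.10 − 0.0953)/0.0742) = 0.52

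**Step 2, what is reported if merged.** B's weight is 200/2200 = 0.091. The merged log HR relative to A averages 0.091 × 0.0953 = 0.0087, an HR of 1.009 where B's true value is 1.10. It misses B's value by 0.0953 − 0.0087 = 0.0866. Its SE is √(1/2200) = 0.0213, so the 99% half-width is 0.0549. The miss exceeds the half-width, and the merged interval covers B's true HR only 7% of the time.

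**Step 3, overall coverage for B.** Add the merged part (chance of merging × 0.068) to the part where B stays separate and its own interval covers:
- (i) 0.062 + 0.093 = 0.16
- (ii) 0.051 + 0.245 = 0.30
- (iii) 0.036 + 0.471 = 0.51

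A simulation with 400 000 replicates gives the same three values.

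**Step 4, other assumed sizes.**

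| Stoppers A/B | True ratio | Merged (i / ii / iii) | 99% interval coverage for B (i / ii / iii) |
|---|---|---|---|
| 2000/200 | 1.00 | 99% / 95% / 82% | 98.4% / 98.1% / 98.2% |
| 2000/200 | 1.10 | 90% / 75% / 52% | 16% / 30% / 51% |
| 2000/200 | 1.20 | 55% / 31% / 13% | 45% / 69% / 86% |
| 500/200 | 1.10 | 92% / 79% / 51% | 79% / 82% / 88% |
| 2000/1000 | 1.10 | 55% / 31% / 55% | 55% / 74% / 55% |
| 2000/1000 | 1.20 | 2% / 0.3% / 2% | 97.7% / 98.8% / 97.6% |

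Pre-specified separate categories would give 99% throughout.

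**The case against.** The case on the other side has five parts.

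- **Clinical similarity is also required.** A reader might infer that any categories with similar HRs will be merged. The article does not support that. The condition narrows the candidates, but adjacent smoking levels and related ethnic groups plainly qualify, and among these the fitted risk decides.
- **Similar need not mean not significantly different.** The wording suits a judgement of size at least as well. That is a fair reason to show a range. Under reading (iii) merging is much less frequent in the main scenario, yet coverage for the small group is still about half.
- **The cohort is large.** If half of the patients stop (an assumption), the secondary prevention cohort has 75 000 stoppers, and a smoking level holding 5% of them has 3750. Two such levels with a true ratio of 1.10 would merge only 6% of the time under reading (i). So smoking is largely unaffected under a test-based rule. Under reading (iii) they would merge 58% of the time, but with equal sizes the merged HR lies midway, about 1.05 from either level, so the distortion is limited.
- **Unmerged descriptive results are planned.** A reader might infer that a distinctive group would vanish from the report. Crude rates by ethnic group, Kaplan-Meier curves and log-rank tests make that unlikely. But they are unadjusted, and smoking is not among the factors listed for the rates.
- **The rule is declared beforehand and the model is exploratory.** Nothing says that merged categories will be presented as fixed in advance. Declaring a data-driven rule makes it transparent but does not restore the interval's level, and the article does adopt a 1% level to protect its inferences.

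The first four narrow the point. None removes it.

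**Conclusion.** The point holds in a limited form. The article makes the coding depend on fitted associations among clinically similar categories. It makes no allowance for that, and none of its additional or sensitivity analyses is described as keeping the listed categories.

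The consequence is material for a small category with a modest true difference from a larger neighbour, which chiefly means rare ethnic groups and mostly the secondary prevention cohort. In the main scenario coverage is 16% to 51% instead of 99%. It is about 1 point or less where the categories truly do not differ, and about 1 point for 2000 versus 1000 stoppers at a ratio of 1.20. These sizes rest on assumed stopper counts, true ratios and readings of similar, since the article gives none of them.

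A reader might infer that the smoking and ethnicity results are generally unreliable, or that the statin-type comparisons are affected. Neither follows: large categories with clear differences are rarely merged, and statin type is not named in the rule. This is an inexpensive improvement, not a fault that threatens the study's main results.

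**What to change.** Keep the ethnicity and smoking categories listed under Covariates in the main Cox model. If some are too small to stand alone, fix the merged groups in advance on clinical grounds and a minimum count, without sight of the HRs. Use the same groups in both prevention cohorts and in all sensitivity analyses. Treat clinically similar variables the same way.

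If outcome-based merging is kept, define what counts as similar and report the unmerged adjusted HRs alongside the merged ones.

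The cost is a change of wording, wider intervals for a few small categories and a slightly longer table. No further data are needed.

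### Five imputations with testing at the 1% level leave the results for the imputed covariates valid, but less precise and less reproducible than they need be, by an amount that depends on the unstated missing fraction

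*Protocol article*

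**What the plan says.** The Statistical analysis section names BMI, smoking status, systolic blood pressure and cholesterol/HDL ratio as variables that "have non-negligible numbers of missing data, multiple imputation will be used to replace missing values". The number of imputations is fixed: "Five imputed data sets will be created, using multiple chained equations". Pooling is by Rubin's rules, and these "rules will be used to combine effect estimates and SEs to allow for uncertainty due to imputing missing values". The imputed analysis is the primary one: "The main analyses will be run using the multiply imputed data". A complete-case check accompanies it: "we shall also run a sensitivity analysis including only patients with complete data".

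One variable is singled out: "The least complete data are expected to be for cholesterol/HDL ratio, but information about this test is expected to be important for patient adherence".

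The end of the Sensitivity analyses section sets the threshold: "A 1% level of statistical significance will be used to allow for multiple comparisons". The article does not say how the figure of five was chosen, and it gives no percentage missing for any variable.

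**The concern.** Five imputations are often defended by the efficiency of the point estimate, which is high even for small m. That leaves out two other costs.

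- **Width.** Under Rubin's rules the interval uses a t distribution whose degrees of freedom depend on m and on the FMI. With m = 5 they can be small. A 1% critical value lies further into the tail than a 5% one, so it suffers more.
- **Reproducibility.** The pooled estimate and its standard error both carry Monte Carlo error. Rerunning the imputation with another seed changes the p-value.

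Both costs fall on the coefficients of the imputed covariates. Cholesterol/HDL ratio is the most exposed, because the article expects it to be the least complete and also expects it to matter for adherence. A large cohort does not remove the problem, because the FMI does not shrink as the number of patients grows.

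**Working it through.** **The plan's own figures.** The article gives no calculation behind m = 5. It also does not say whether the 1% level is one- or two-sided. The Sample size calculation section settles that. With a two-sided 1% level, 90% power and equal allocation:

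- 4 × (2.576 + 1.282)² / (ln 0.9)² = 5362
- 4 × (2.576 + 1.282)² / (ln 0.8)² = 1196

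Both equal the stated figures, so two-sided 1% tests, and hence 99% intervals, are used below.

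**Inputs.** m = 5 and pooling by Rubin's rules (Statistical analysis); 1% level (Sensitivity analyses). The FMI is an assumption, shown over a range, because the article describes missingness only in words.

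**Formulas.** Scale the variance so that with unlimited imputations it equals 1: within-imputation W = 1 − FMI, between-imputation B = FMI. Then

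- T = W + (1 + 1/m)B
- r = (1 + 1/m)B / W
- df = (m − 1)(1 + 1/r)²
- relative 99% width = t(0.995, df) × √T / 2.576

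**Example, FMI 0.3, m = 5.** T = 0.7 + 1.2 × 0.3 = 1.06. r = 0.36/0.7 = 0.514. df = 4 × (1 + 1/0.514)² = 34.7. t = 2.725. Width = 2.725 × 1.030 / 2.576 = 1.089.

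**99% width relative to unlimited imputations**

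| FMI | df at m = 5 | m = 5 | m = 20 | m = 50 |
|---|---|---|---|---|
| 0.05 | 1133 | 1.007 | 1.002 | 1.001 |
| 0.1 | 289 | 1.017 | 1.004 | 1.001 |
| 0.2 | 75 | 1.046 | 1.009 | 1.004 |
| 0.3 | 34.7 | 1.089 | 1.017 | 1.007 |
| 0.5 | 13.4 | 1.220 | 1.040 | 1.015 |

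For a 95% interval at m = 5 the ratios are 1.067 at FMI 0.3 and 1.152 at FMI 0.5. The stricter level does make the cost larger.

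**Reproducibility.** Take one data set in which a covariate would have z = 2.8 (p = 0.005) with unlimited imputations, and re-impute it many times. The estimate varies with SD √(B/m), and the estimated B varies as a scaled chi-square on m − 1 degrees of freedom. Simulation (200 000 re-imputations) gives:

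| FMI | m | p-value, 5th to 95th percentile | share with p < 0.01 | CV of 99% width |
|---|---|---|---|---|
| 0.1 | 5 | 0.0023 to 0.015 | 83% | 5% |
| 0.1 | 20 | 0.0034 to 0.0081 | 99% | 2% |
| 0.3 | 5 | 0.0008 to 0.049 | 56% | 17% |
| 0.3 | 20 | 0.0021 to 0.014 | 84% | 5% |
| 0.5 | 5 | 0.0003 to 0.094 | 43% | 28% |
| 0.5 | 20 | 0.0014 to 0.023 | 69% | 9% |
| 0.5 | 50 | 0.0022 to 0.013 | 87% | 5% |

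At m = 5 the Monte Carlo SD of the log HR, √(FMI/5), is 14% of its standard error at FMI 0.1, 24% at 0.3 and 32% at 0.5.

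**The case against.** **Rubin's rules are valid with five imputations.** This stands. The wider t quantile is there to keep coverage right. A reader might infer bias or an inflated type I error; nothing here supports that.

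**The missing fraction is unknown.** This also stands. A reader might infer that intervals for every incompletely recorded covariate are noticeably wider. At FMI 0.05 the excess is 0.7% and at 0.1 it is 1.7%; it becomes noticeable only from about 0.2 to 0.3. The article makes a high value plausible for cholesterol/HDL ratio only by calling it the least complete.

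**The cohort is very large.** In absolute terms the loss is small. As an illustration, take the secondary prevention group of 150 000 (one-quarter of 600 000) and assume 40% discontinue, one standardised covariate, FMI 0.5, and no clustering or collinearity. The complete-data SE is 1/√60 000 = 0.0041 and the total SE is 0.0041/√0.5 = 0.0058. For HR 1.05 the 99% interval is about 1.031 to 1.069 with m = 5 and 1.034 to 1.066 with m = 40. So mainly borderline results are at risk, although rare categories of an imputed variable would have wider intervals than this. The comparison used for the sample size is statin type, which is not imputed. What does not follow is that the noise vanishes: relative to the standard error it is the same at any cohort size.

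**A complete-case analysis is planned.** It addresses robustness to the imputation, but does not reduce Monte Carlo error in the main analysis.

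**Two further readings go too far.** At FMI 0.5 the width ratio of m = 5 to m = 40 is 3.142/2.625 = 1.197, and 1 − 1/1.197² = 30%, so one might say 30% of the information is discarded. That is only a squared-width equivalent. The efficiency of the estimate itself is (1 + 0.5/40)/(1 + 0.5/5) = 0.92, a loss of about 8%; the rest comes from the larger t quantile. One might also count the QRISK2 bands among the affected terms, but the article neither lists the score's inputs nor says how the score is handled when values are missing.

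**Conclusion.** The point holds as a minor, inexpensive improvement. Five imputations with 1% tests give valid inference that is less precise and less repeatable than it could be for cholesterol/HDL ratio, BMI, smoking and systolic blood pressure. The lost precision is negligible at FMI 0.1 or below and material from about 0.3 upward. Reproducibility is the stronger part: even at FMI 0.1, about one re-imputation in six would move a p-value of 0.005 to 0.01 or above. All sizes rest on an assumed FMI, on two-sided 1% tests and on the usual Rubin approximation. Covariates that are not imputed should be little affected, since their FMI will usually be low.

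**What to change.** Replace the fixed five with at least 20 imputations, or set the number from the data at about 100 × the largest observed FMI. Where that FMI exceeds 0.2 the second rule asks for more than 20, and the rows for FMI 0.5 show why it is worth following. Report the FMI for each imputed covariate and the Monte Carlo error of the pooled log HRs, so that readers can see whether a result near p = 0.01 is stable.

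The cost is computing time: at least four times the imputation and model fitting (20/5 = 4), on about 600 000 records split into two groups. It is not confined to a single run. The imputation model contains stopper status and log survival time, so planned reruns that change the outcome, the follow-up or the cohort may need fresh imputation. Candidates are the analysis including one-prescription patients, the two first-year analyses, the 365-day outcome and the 5-year restriction. Data collection, outcome definition and the Cox model are unchanged.
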